#### **8.4. Pharmacokinetic Assessment**

Patients receive HA121-28 treatment after the implementation date of the revised protocol (V3.0) will undergo PK blood collection at any time point 4-8 hours after C1D1, before C1D15 ( $\pm 1$  day) (-30 min), 4-8 hours after dosing (if applicable), or on C1D28 ( $\pm 3$  days), C2D28 ( $\pm 3$  days), C4D28 ( $\pm 3$  days), C6D28 ( $\pm 3$  days) after dosing. For patients enrolled before the execution date mentioned above and have not terminated treatment, PK sampling can be performed at any point during any two visits of C1D15 ( $\pm 1$  day) before (-30 min) and 4-8 hours after dosing, and CnD28 ( $\pm 3$  days). If a patient terminates treatment during the study, a blood sample can be collected for PK analysis on the day of the EOT visit as appropriate. 3ml of blood should be collected each time, and plasma should be separated for HA121-28 concentration determination. Please refer to the relevant operation manual for the processing and storage of blood samples. The actual sampling time will be recorded in the original medical record and eCRF, and used for calculation of relevant parameters.

## 9. Statistical Considerations

The detailed summary and statistical analysis methods for the data collected in this study will be included in the Statistical Analysis Plan (SAP), which will be finalized after we complete the protocol and CRF but before we lock the database. The SAP will contain detailed information about all the statistical analyses that will be performed based on the main features of the protocol. If there are any changes to the protocol that are deemed to have a significant impact on the SAP by the sponsor or principal investigator, the SAP will need to be revised to maintain consistency with the study protocol.

### 9.1. Statistical Assumptions

This study is based on the evaluation of objective response rate (ORR) to assess efficacy. The hypothesis is that the efficacy of HA121-28 tablets is superior to the ORR of the historical control group.

$H_0: \pi \leq \pi_0$ ;

$H_1: \pi > \pi_0$ ;

PI 0: Historical control group for the ORR of second-line or above treatment in NSCLC with RET fusion.

A: HA121-28 tablets for the treatment of second-line or above NSCLC with RET fusion, with the ORR as the primary endpoint.

### 9.2. Sample Size Estimation

This study has a single-arm design, with the main efficacy measure being ORR. From a clinical perspective, an ORR of 30% or higher as the treatment of second-line or higher RET fusion NSCLC is considered clinically significant. Assuming that the ORR of HA121-28 tablets for the treatment as second-line or higher RET fusion NSCLC is 45%, with a one-sided significance level of 0.025 and a power of 80%, the sample size is estimated to be 83 using the single-group target value method. The study is indicated as successful, when at least 34 patients show improvement, corresponding to an ORR of 41%, the lower limit of the 95% confidence interval can be greater than 30%.

**Table 9-1 Sample Size Estimation**

| Drug ORR Assumptions | Control criteria (Lower 95% confidence interval) | Sample Size | Minimum number of responses | Response Boundary | 95% confidence interval (Clopper-Pearson) |
|----------------------|--------------------------------------------------|-------------|-----------------------------|-------------------|-------------------------------------------|
| 45%                  | 30%                                              | 83          | 34                          | 41.0%             | (30.28%,52.31%)                           |

Sample size estimation will be performed using nQuery 8.

### 9.3. Analysis of Population

- Full Analysis Set (FAS): Includes all patients who have been enrolled and received at least one dose of the study treatment. FAS is used for demographic, baseline characteristics, and efficacy analysis.
- Per Protocol Set (PPS): Refers to a subset of patients in a clinical study who strictly adhere to the study protocol without any major protocol violations. PPS is used for sensitivity analysis and includes all patients from the full analysis set who meet the criteria for PPS.
- Safety Set (SS): Includes all patients who have received at least one dose of the study treatment.
- Pharmacokinetic Concentration Set (PKCS): Refers to a group of patients who have received at least one dose of the study treatment and have at least one assessable PK concentration without any significant deviation from the dosing regimen.

### 9.4. Statistical Analysis

#### 9.4.1. General Methods

The statistical analysis of this study will be conducted using SAS 9.4 or higher version.

For the statistical description of categorical variables will be expressed in terms of the number of cases and percentage. For the statistical description of continuous variables includes the number of cases, mean, standard deviation, median, lower quartile, upper quartile, minimum value, and maximum value. Unless otherwise specified, a two-sided test will be used with a significance level of 0.05, and a 95% confidence interval will be used for parameter estimation.

#### 9.4.2. Participant Disposition

- Summarize the information on patient enrollment, completion, withdrawal, protocol violations, and data set allocation.

- Plot a flow chart of patient disposition;
- Make lists to describe detailed information on the patients' enrollment, completion or withdrawal from the study, protocol violations, and data set division.

#### **9.4.3. Demographic and Baseline Analyses**

- The FAS set will be used for analysis;
- Statistically describe the baseline characteristics of the patients, including demographics, medical history, and other relevant factors.
- Calculate the sample size, mean, standard deviation, median, lower quartile, upper quartile, minimum value, and maximum value for continuous variables.
- The number and percentage of patients will be calculated with number and grade data.

#### **9.4.4. Efficacy Analysis**

- Primary endpoint measures
  - The analysis will be performed based on FAS and PPS;
  - Calculate the objective response rate (ORR) assessed by IRC assessment and calculate the 95% confidence interval using the Clopper-Pearson method.
- Secondary efficacy measures
  - Analysis will be performed based on FAS;
  - Determine the median time and 95% CI for PFS, DOR, and OS assessed by IRC and investigator using the Kaplan-Meier method. Plot corresponding survival curves;
  - Calculate the ORR assessed by investigators and the DCR assessed by both the IRC and investigator. Calculate the 95% confidence interval using the Clopper-Pearson method.

#### **9.4.5. Pharmacokinetic Analysis**

- Analysis based on PKCS;
- Collect PK samples at the designated time points according to the protocol, and measure the concentration of HA121-28 in plasma. Conduct a tabular and descriptive statistical analysis of the HA121-28 concentration;

- If there is sufficient data, the blood drug concentrations of the patients mentioned above will be analyzed using a nonlinear mixed-effects model (NONMEM) for population pharmacokinetic (PPK) analysis. The analysis report and details can be found in a separate report;
- The specific statistical analysis contents are detailed in the statistical analysis plan.

#### **9.4.6. Safety Analysis**

- Analysis based on SS;
- Summarize the number and percentage of Treatment-emergent Adverse event (TEAE)/treatment-related TEAE, SAEs/treatment-related SAEs, TEAE leading to discontinuation/treatment-related TEAE leading to discontinuation during the course of treatment;
- Summarize the number and percentage of TEAEs/treatment-related TEAEs, SAEs/treatment-related SAEs, TEAEs leading to discontinuation/treatment-related TEAEs leading to discontinuation, based on SOC/PT;
- Summarize the incidence and percentage of TEAEs/treatment-related TEAEs, SAEs/treatment-related SAEs, TEAEs leading to discontinuation/treatment-related TEAEs leading to discontinuation by SOC/PT and severity;
- Provide a detailed list of TEAEs/Treatment-related TEAEs categorized by SOC/PT and severity;
- Laboratory indicators: Provide a cross table for clinical judgment before and after medication, and conduct a descriptive and diachronic analysis of the measured values and changes from the baseline of laboratory test measures before and after medication. Provide a detailed list of examination results;
- Electrocardiogram: Provide a cross-tabulation of clinical judgments before and after medication, and perform descriptive and longitudinal analyses of the measured values and changes from baseline of electrocardiogram measures at each time point before and after medication. Provide a detailed list of the examination results;
- Physical examination: Provide a cross-tabulation of clinical assessments before and after medication, and provide a detailed list of examination results;

- Vital signs: Descriptive and longitudinal analyses will be performed on the measured values and changes from the baseline of various measures before and after medication. A detailed list of examination results before and after medication will also be provided.

#### **9.4.7. Analysis of Concomitant and Non-drug Therapies**

- Analysis will be performed as per SS;
- Concomitant medications will be summarized by ATC classification;
- Non-drug therapies will be summarized by SOC and PT;
- Details of concomitant and non-drug therapies will be tabulated.

#### **9.4.8. Analysis of Drug Exposure and Compliance**

- Perform the analysis as per SS;
- Drug exposure includes the duration of drug exposure, the total amount of drug used, and the average daily dose. The number and proportion of patients, who have dose reduction, temporary discontinuation, and permanent discontinuation of drug administration, will be listed and analyzed in this study;
- The duration of drug exposure will be calculated in days using the following formula:
  - Exposure will be considered missing if the start or end date is missing. Exposure is calculated as the last date of medication use minus the first date of medication use plus one, minus the number of days of missed or paused medication during that period;
- The average daily dose is defined as the total amount of drug used divided by the drug exposure time;
- Medication adherence is defined as the actual amount of medication used divided by the planned amount of medication to be used, multiplied by 100%;
- Calculation of total drug amount: Sum of planned daily drug dosage during the medication period;
- Calculation of actual drug usage: the sum of the actual daily dosage during the medication period.

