### 6.1.2. Dosing Regimen of Study Treatment

The recommended starting dose is 450 mg. It should be administered once daily for 21 consecutive days, followed by a 7-day drug-free period. Each cycle lasts 28 days and the medication should be taken orally with warm water.

During the treatment period, the investigator may adjust the dosage based on the patient's tolerance.

The time and dose of administration will be recorded in detail in the diary card.

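### Section 9.4.8 gives the total that feeds average daily dose a planned-dose definition and does not settle which days count, so the exposure summary can mislead

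*Protocol*

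**What the plan says.** Section 9.4.8 names three exposure measures: "Drug exposure includes the duration of drug exposure, the total amount of drug used, and the average daily dose". It then gives formulas.

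- Average daily dose: "The average daily dose is defined as the total amount of drug used divided by the drug exposure time".
- Exposure time: last dosing date minus first dosing date plus one, "minus the number of days of missed or paused medication during that period".
- Adherence: "Medication adherence is defined as the actual amount of medication used divided by the planned amount of medication to be used, multiplied by 100" (per cent).
- A planned sum: "Calculation of total drug amount: Sum of planned daily drug dosage during the medication period".
- An actual sum: "Calculation of actual drug usage: the sum of the actual daily dosage during the medication period".

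The same section also reports how many patients had dose reductions, temporary stops and permanent stops.

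Section 6.1.2 sets the regimen: "The recommended starting dose is 450 mg", taken "once daily for 21 consecutive days, followed by a 7-day drug-free period". Section 6.1.3 allows a reduction to 300 mg. Note [2] to the schedule in section 1.2 sends a patient who has been off drug for 7 days or more straight to the next cycle on resuming.

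**The concern.** The word *total* appears in an exposure measure, in the numerator of average daily dose, and in the label of the planned sum. The actual sum carries a different label. A programmer who matches labels would put planned doses over a day count from which missed and paused days have been removed. The result is neither a mean dose taken nor a dose intensity.

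Choosing the actual sum does not settle the denominator. It drops the days on which a patient failed to take a due dose. On an ordinary reading it keeps the drug-free week, when no dose was due.

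The exposure summary tells the reader how much drug lies behind the safety results and behind the response rate at a 450 mg starting dose. Two programmers could follow section 9.4.8 in good faith and report materially different averages.

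**Working it through.** The protocol states no numerical exposure result, so there is no figure to reproduce. The check applies its formulas to assumed dosing histories.

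**Inputs.** Starting dose 450 mg and 21 days on, 7 days off (section 6.1.2); reduced level 300 mg (section 6.1.3); formulas from section 9.4.8. The pause is set at 5 days, so that the 7-day rule in schedule note [2] does not apply.

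**One cycle (21 dosing days).** The planned sum is 21 × 450 = 9450 mg.

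*History A: 8 days at 450 mg, 5 days paused, 8 days at 450 mg.* The actual sum is 16 × 450 = 7200 mg, and exposure time is 21 − 5 = 16 days.

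*History B: 8 days at 450 mg, then 13 days at 300 mg, no pause.* The actual sum is 3600 + 3900 = 7500 mg, and exposure time is 21 days.

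| History | Planned sum / exposure days | Actual sum / exposure days | Actual sum / scheduled dosing days |
|---|---|---|---|
| A, 5-day pause | 9450/16 = 590.6 | 7200/16 = 450.0 | 7200/21 = 342.9 |
| B, reduction after Day 8 | 9450/21 = 450.0 | 7500/21 = 357.1 | 7500/21 = 357.1 |

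All entries are mg/day. In the planned column, A exceeds the highest dose taken and B shows no reduction. In the actual column, B is right, but A looks the same as perfect dosing.

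**Conditions on the planned column.** The 590.6 needs planned doses on paused days to be counted; otherwise the sum is 7200 mg and the result 450.0. The 450.0 for B needs the planned dose to stay at 450 mg after the reduction; if it resets to 300 mg, the planned sum is 7500 mg and the result 357.1. Section 9.4.8 settles neither.

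**Several cycles, full compliance at 450 mg.** With c cycles, and the last dose on Day 21 of the last one, the calendar span is 28(c − 1) + 21 = 28c − 7 days. If the drug-free days are not subtracted, the average is 450 × 21c / (28c − 7):

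- 1 cycle: 9450/21 = 450.0
- 2 cycles: 18900/49 = 385.7
- 6 cycles: 56700/161 = 352.2
- 12 cycles: 113400/329 = 344.7

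If those days are subtracted as paused, the average is 450 throughout. At 6 cycles the choice moves the figure by 450.0 − 352.2 = 97.8 mg/day. Without subtraction, history B over a single cycle (357.1) scores higher than a fully compliant patient at 6 or 12 cycles.

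**Limit on the overshoot.** If the drug-free days stay in the denominator, the planned-sum average exceeds 450 only when paused days number more than 49 − 42 = 7 over 2 cycles, or more than 161 − 126 = 35 over 6. The 590.6 is therefore a short-treatment result, unless the drug-free days are subtracted.

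**The case against.** The best counter-argument rests on the order of the text. The planned and actual sums come directly after adherence, which is actual over planned, so they can be read simply as its denominator and numerator. The word *used* in the average daily dose then points to the actual sum. On that reading the average shows every reduction and cannot exceed the highest dose taken. This is a fair reading and may be the intended one. A reader might infer that the protocol definitely feeds planned doses into the average; the text does not go that far. It leaves two readings open, and the labels favour the less sensible one.

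Second, mean dose per day on drug is a legitimate summary, and the protocol does not call it dose intensity. Interruptions are also visible elsewhere, in the counts of temporary stops and in adherence: 7200/9450 = 76.2% for history A, if planned doses on paused days count. That stands as partial compensation. The average still cannot show how far pauses lowered the dose delivered.

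Third, the section does not say that drug-free days are not paused days. That is true. But a scheduled break is not, in ordinary use, a missed or paused dose, and if it were counted as one, the protocol would need to say so.

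Fourth, the protocol leaves detailed methods to the SAP. Here, however, it states formulas itself, so an SAP that follows it takes over the conflict.

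**Conclusion.** The point holds as a conflict of labels and an unresolved day count in formulas that the protocol itself states. The planned-sum results (590.6 for the pause; 450.0 instead of 357.1 for the reduction) depend on the literal reading and on the conditions set out in the working. With actual doses as numerator, two weaknesses remain: pauses do not show (450.0 against 342.9 mg per scheduled dosing day), and the average falls with time on treatment in a fully compliant patient, to 344.7 mg/day at 12 cycles, unless drug-free days are treated as paused.

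A reader might infer that the efficacy conclusion is at risk. The documents do not support that. Success rests on at least 34 responders among 83 patients and on the Clopper-Pearson limit, and average daily dose enters no decision. Nor should an inflated average be set against the phase 1 maximum tolerated dose: it is an arithmetical artefact, not a dose that anyone took. Only descriptive exposure summaries are affected. The correction should still be made, because it improves a reported number at very little cost.

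**What to change.** Amend section 9.4.8, and carry the same wording into the SAP:

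1. Define total amount used as the sum of actual daily doses, and use it as the numerator of average daily dose.
2. Name the planned sum as the adherence denominator only. State whether it resets after a dose reduction and whether it counts doses due on paused days.
3. Divide by the scheduled dosing days between first and last dose: exclude the scheduled drug-free days, include missed and paused days. Ending the count at the last dose covers patients who stop mid-cycle. State how interruptions of 7 days or more count, consistently with schedule note [2].
4. Report relative dose intensity over the same days. Taken against the 450 mg starting dose, it would be 7200/9450 = 76.2% for history A and 7500/9450 = 79.4% for history B.
5. Report calendar time on treatment as a separate measure.

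The cost is a few lines of wording and minor programming. Diary cards (section 6.1.2) and pill counts (section 6.4) already supply the data.

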#### **9.4.9. Planned Interim Analyses**

Not applicable.

#### **9.4.10. Subgroup Analysis**

Not applicable.

#### **9.4.11. Multiplicity Issues**

Not applicable.

#### **9.4.12. Exploratory Analyses**

Not applicable.

### **10. Supporting Documentation and Operational Considerations**

#### **10.1. Regulatory, Ethical, and Study Regulatory Considerations**

##### **10.1.1. Informed Consent Process**

##### **10.1.1.1. Informed Consent Form and Other Documents Provided to Patients**

The informed consent form is an important document that provides detailed information about the study intervention, procedures, and risks. It must be reviewed by an ethics committee and written consent must be obtained before starting the study intervention. During the study, other study documents may also be provided to the patients to collect information, including but not limited to patient diaries.

##### **10.1.1.2. Informed Consent Process and Documentation**

Informed consent is a process that begins before an individual agrees to participate in a study and continues throughout their participation. The informed consent document must be approved by an Institutional Review Board (IRB) and patients will be asked to read and review the document. The investigator will explain the study to the patient, including the purpose, procedures, potential risks, and the patient's rights, in a way that is understandable to them and answer any questions they may have. Patients should have adequate time to read and ask questions before signing the written informed consent document. Patients should have the opportunity to discuss the study with family or a representative or consider it themselves before agreeing to participate. The informed consent document must be signed by the patient before

any study procedures are performed. Patients must be informed that participation in the study is voluntary and they can withdraw at any time without harm. The investigator will provide the patient with a copy of the informed consent document for their retention. The informed consent process should be conducted before any study procedures are performed and documented in the source file (including the date) along with the signed informed consent document. The investigator must inform the patient that "refusal to participate in this study will not adversely affect the quality of their medical care" to ensure the patient's rights and welfare.

### **10.2. Study Suspension and Discontinuation**

If there are sufficient and reasonable reasons, this study may be temporarily suspended or terminated early. The party responsible for suspending or terminating the study should provide written notice to the investigator, sponsor, and ethics committee, as well as record the reasons for the suspension or termination of the study. If the study is terminated early or temporarily suspended, the principal investigator should promptly notify the patients, ethics committee, and sponsor, and provide the reasons for the termination or temporary suspension of the study. The investigator will contact the patients and notify them of changes to the visit schedule (if applicable).

### **10.3. Confidentiality and Privacy**

The confidentiality and privacy rights of the patients will be strictly protected by the participating investigators, their staff, and the sponsor and its interventions. This confidentiality will extend not only to clinical information related to the patients but also to tests involving biological sample testing and genetic testing. Therefore, the study plan, documents, data, and all other information generated during the study will be kept strictly confidential. Any information or data related to the study may not be disclosed to unauthorized third parties without the written permission of the sponsor.

All study activities will be conducted in a private setting as far as possible.

Clinical research associate (CRA), other authorized representatives of the sponsor, representatives of the Institutional Review Board (IRB), regulatory authorities or the pharmaceutical company providing the study product may inspect all documents and records

that need to be kept by the study patients, including but not limited to medical records (office, clinic, or hospital) and pharmacy records of the study patients. The clinical study site should allow access to these records.

The contact information of the patients will be securely stored at each clinical study center for internal use during the study. At the end of the study, all records will continue to be stored in a secure location for a duration longer than the time required by IRB review, institutional regulations, or sponsor requirements.

